**Figure1: Parasite prevalence in the Kilimanjaro region**

[figure not shown]

Source: Drakeley C, Reyburn et al. MIM conference abstract no. 318, Arusha, Tanzania

malariometric survey in 2002 showed significant variation in the prevalence of malaria parasitaemia in <5 year old children at different levels of altitudes within and between the

districts (Figure 2). The survey was conducted in four groups of villages: Rombo (purple), South Pare (pink), Western Usamabara (yellow) and Eastern Usambara (grey). The relationship between the mean altitude of the village and the prevalence of parasitaemia is shown in the graph (insert). The mean altitude of villages within in each group ranged from 200 to 1800 meters. The prevalence of malaria parasite in 0-4 year old children ranged from 20% to 55% in the lowlands (<750m) and from 1% to 20% at 1000-1500m altitude. The malaria transmission pressure in lowland villages in the South Pare district is low/moderate. The prevalence of malaria parasitaemia was 30% in 1-4 year-old children and 4% in <1 year-old infants. The prevalence of parasitaemia was higher in Western Usambara villages (52% in 1-4 year-old children and 20% in <1 year-old infants).

The advantages of the study site for the proposed trial are:-

1. Levels of resistance to SP and amodiaquine are high and so investigation of alternative drugs that could be used for IPTi is needed urgently and can be justified ethically.
2. A wide range of levels of malaria transmission are found over a small area in a homogeneous population.
3. The epidemiology of malaria in the study area has recently been carefully defined.

Although detailed epidemiological studies have recently been undertaken in the study area, it will be necessary to confirm that major differences persist between highland and lowland sites during the period of the trial. We have considered the possibility of making direct measurements of EIR but this is difficult and expensive in low transmission areas because of the paucity of anopheline mosquitoes and the low sporozoite rate. In a recent study in Hai district, Tanzania, 2198 anopheline mosquitoes were collected over a period of 12 months and only 8 mosquito were infected giving an EIR with very wide confidence limits. Instead of EIR estimates, we will rely upon the prevalence of infection in nine month old infants in the placebo groups to estimate the force of infection in the two sites.

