**4.4. Sample size**

The number of infants per arm needed for a study with 80% power and 95% significance for the primary and secondary outcome measures in the low/moderate transmission site

(South Pare) is shown in Table 6a. The required sample size was calculated using STATA software and based on the following assumptions:

1. the incidence of clinical malaria and anaemia in the placebo group in this setting will be similar to that observed by Schellenberg et al in Ifakara, Tanzania in 1999-2000;13
2. The effect of IPTi with mefloquine on clinical malaria and anaemia is similar to that of IPTi with SP observed by Schellenberg et al.;13
3. The effect of IPTi with Lapdap on clinical malaria and anaemia will be 50% less than the effect of mefloquine because Lapdap has little or no chemoprophylactic effect;
4. The effect of IPTi with SP on clinical malaria and anaemia will be 50% less than the effect of mefloquine because the resistance to SP in this setting is expected to be 50%.

Low transmission site: For the comparison of the primary outcome measure, the highest number infants (551) needed is for the comparison of the incidence of malaria between placebo and Lapdap groups. Allowing for 10% loss to follow up, 610 infants per arm i.e. a total of 2440 infants would be needed for the study in the South Pare district (see table 6a).

This sample size will have the power (90%) to detect a difference of 0.5g/dl Hb or less between the mefloquine and Lapdap arms, and also to detect a difference of 0.5g/dl between all treatment arms and placebo.

**Table 6a:** Estimates of the incidence or prevalence of primary and secondary outcomes in the comparison groups and the sample sizes required for a study in South Para area (low/moderate transmission)

| Endpoints | Expected rate/prevalence | | | Sample size per arm needed for a study with 80% power and 95% significance | | |
| --- | --- | --- | --- | --- | --- | --- |
|  | Placebo group | MQ group | Lapdap and SP groups | Placebo versus  MQ group | Placebo versus Lapdap or SP group | MQ versus  Lapdap or SP group |

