| **Primary**   1. Incidence of clinical malaria in infants   **Secondary**   1. Mean Hb at 10 months of age 2. Incidence of severe anaemia in infants 3. Prevalence of parasite at 10 months of age 4. Risk of clinical malaria at 12-23 months | 0.40/child/yra  9.5 gm/dlc  0.16/child/yra  30%c  0.40/childf | 0.20/child/yra  10.5 gm/dld  0.08/child/yra  15%e  0.56/childg | 0.30/child/yrb  10.0 gm/dlb  0.12/child/yrb  20% e  0.48/childh | 118  63  295  121  295 | **551**  252  1,377  294  628 | 393  252  984  908  636 |

aBased on estimates from Ifakara in 1999-2000 (Schellenberg et al) in the placebo and SP groups.

bAssumes that the effect of Lapdap on clinical malaria and anaemia will be 50% less than MQ because Lapdap has very little or no chemoprophylactic effect and that the effect of SP will also be 50% less than MQ because the resistance to SP in this area is 50%.

cBased on estimates from surveys done in Kilimanjro region in 2001-2002 (MRC-1 and Hai projects - unpublished).

d50% reduction in the incidence of severe anaemia was based on the observation in Ifakara in 1999 and it is assumed that this would increase the mean Hb at 10 months of age by 1 gm/dl.

e Assumes that the reduction in the prevalence of parasitaemia at 10 months of age would be similar to the reduction in the incidence of clinical malaria.

fAssumes that the incidence of malaria in the second year of life would be similar to the first year and that 25% of these infection will be severe.

gAssumes that incidence of malaria in the MQ group will increase by 40% in the second year of life

hAssumes that the incidence of malaria in the Lapdap and SP groups will increase by 20% in the second year of life.

The number of infants per arm needed for a study with 80% power and 95% significance for the primary and secondary outcome measures in the high transmission site (Western Usambara) is shown in Table 6b. For the comparison of the primary outcome measures, the highest number infants (291) needed was for the comparison of incidence of malaria between placebo and Lapdap groups. Allowing for 10% loss to follow up, 320 infants per arm ie. a total of 1280 infants would be needed for the study in the Western Usambara district.

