For the comparison of the incidence of clinical malaria in the second year of life (rebound effect) the data from the two sites has to be combined. This combined population would have adequate power to compare the incidence between the placebo group and the mefloquine group. However, this sample size may not be adequate for comparing between the placebo and Lapdap group unless the rebound effect is as high as that in the mefloquine group.

**Table 6b:** Estimates of the incidence or prevalence of primary and secondary outcomes in the comparison groups and the sample sizes required for a study in Western Usambara area (high transmission)

| Endpoints | Expected rate/prevalence | | | Sample size per arm needed for a study with 80% power and 95% significance | | |
| --- | --- | --- | --- | --- | --- | --- |
|  | Placebo group | MQ group | Lapdap and SP groups | Placebo versus  MQ group | Placebo versus  Lapdap or SP group | MQ versus  Lapdap or SP group |
| **Primary**   1. Incidence of clinical malaria in infants   **Secondary**   1. Mean Hb at 10 months of age 2. Incidence of severe anaemia in infants 3. Prevalence of parasite at 10 months of age 4. risk of clinical malaria at 12-23 months | 0.62/child/yra  9 gm/dlc  0.39/child/yra  40%c  0.62/childf | 0.30/child/yra  10 gm/dl d  0.20/child/yra  20% e  0.86/childg | 0.45/child/yrb  9.5 gm/dlb  0.30/child/yrb  30% e  0.74/childh | 71  63  129  81  59 | **291**  252  670  357  252 | 262  252  393  294  190 |

aBased on estimates from Ifakara in 1995 (Menendez et al) in placebo and Deltaprim groups

bAssumes that the effect of Lapdap on clinical malaria and anaemia will be50% less than MQ because Lapdap has very little or no chemoprophylactic effect and that the effect of SP will also be 50% less than MQ because the resistance to SP in this area is 50%.

cBased on estimates from surveys done in Kilimanjro region in 2001-2002 (MRC-1; unpublished).

d50% reduction in the incidence of severe anaemia was based on the observation in Ifakara in 1999 and it is assumed that this would increase the mean Hb at 10 months of age by about 1 gm/dl.

e Assumes that the reduction in the prevalence of parasitaemia at 10 months of age would be similar to the reduction in the incidence of clinical malaria.

fAssumes that the incidence of malaria in the second year of life would be similar to the first year and that 20% of these infection will be severe.

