# Change in Contact 7 for Low transmission site

Contact 7 at age 18 months will be the last scheduled visit for children at the low transmission site. This is because the low incidence in malaria at the site means that there is a very small chance that this study will detect a rebound effect of malaria even if present.

At the high transmission site, all children will be invited to attend the clinic at the age of approximately 24 months (**contact 8**) and finger prick blood sample will be obtained for screening for malaria using Paracheck dipsticks and also for preparation of blood slides, filter paper samples and Hb. If a child is positive dipstick test is currently febrile (Temp >37.5° C) or has a history of fever with in the past 2 days, and/or has a history of taking SP for a febrile illness during the previous week, the child will be treated with Artemether - Lumefantrine.

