Resistance to SP is linked strongly to mutations in the dihdyrofolate reductase (DHFR) and dihydropteroate synthase (DHPS) genes and resistance to Lapdap is probably also strongly related to mutations in these genes, although this has not been established so clearly. There are no definitive molecular markers for mefloquine resistance although some linkage to mutations in the *Pfmdr* gene has been described (24). In order to define the overall level of resistance to anti-folate drugs in the study area, DNA will be extracted from filter paper blood samples obtained from children in the control group who are parasitaemic when blood samples are collected at 10 months of age and tested for DHFR and DHPS mutations. These parasites will not have been subjected to selection by drugs given for IPTi and should reflect the overall pattern of resistance in the community. With a total of around 930 children in the placebo control and an overall parasite prevalence of 25% there should be around 230 samples available for molecular analysis. Information obtained on the background level of resistance to anti-folate drugs will allow comparisons to be made between the results of this trial and other trials of IPTi which have used, or are using, SP.

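### Section 4.4, Tables 6a and 6b: five of the six second-year sample sizes treat incidence rates as proportions and are 1.7 to 4.6 times too small, and the South Pare parasitaemia row breaks its own footnotes

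*Protocol*

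**What the plan says.** Section 4.4 introduces each table with "The number of infants per arm needed for a study with 80% power and 95% significance". The second-year row, "risk of clinical malaria at 12-23 months" in Table 6b, gives placebo, mefloquine and Lapdap/SP values of 0.62, 0.86 and 0.74 per child, with sizes 59, 252 and 190. Table 6a gives 0.40, 0.56 and 0.48, with sizes 295, 628 and 636. Footnotes f to h derive these values from first-year incidence, increased by 40% for mefloquine and 20% for Lapdap and SP. Section 4.3 defines the outcome as incidence, and Section 6 analyses malaria incidence by Poisson regression.

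On which data answer the question, four places differ:
- The text before Table 6b states, for the second-year comparison: "rebound effect) the data from the two sites has to be combined". It adds that placebo v mefloquine would then be adequately powered and that placebo v Lapdap may not be.
- Section 6 treats the two sites as separate trials.
- Section 4.5 says: "Contact 7 at age 18 months will be the last scheduled visit for children at the low transmission site".
- Section 4.9 follows every enrolled infant to 24 months.

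The Table 6a row "Prevalence of parasite at 10 months of age" plans 30% (placebo), 15% (mefloquine) and 20% (Lapdap/SP), with sizes 121, 294 and 908. Section 3 says of South Pare: "The prevalence of malaria parasitaemia was 30% in 1-4 year-old children and 4% in <1 year-old infants". Section 4.11 assumes "an overall parasite prevalence of 25% there should be around 230 samples available for molecular analysis".

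**The concern.** A rate of 0.62 or 0.86 episodes per child-year is not a probability. A two-proportion formula gives such values the binomial variance p(1 - p), which is well below the Poisson variance at this level, so the required size comes out too small. The printed 252 and 190 both lie below the 288 evaluable infants per arm at the high-transmission site, so Table 6b suggests that this site can answer all three rebound questions alone. If it cannot, an inconclusive Lapdap or SP comparison could be taken as evidence of no rebound. Assessing clinical immunity is one of the four main objectives in Section 2.1.

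The parasitaemia row raises a smaller, similar problem: one planned value contradicts the footnotes beneath it, and the placebo prevalence sits far above the infant figure in Section 3.

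**Working it through.** **Settings.** Two-sided 5% and 80% power, which reproduce the tables: z = 1.960 and 0.842, and (1.960 + 0.842)² = 7.849. Evaluable per arm after 10% loss: 610 × 0.9 = 549 (South Pare) and 320 × 0.9 = 288 (high-transmission site).

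**Formulas.**
- Rates, one year per child: n = 7.849 (r1 + r2)/(r1 - r2)².
- Proportions: n = [1.960√(2p(1 - p)) + 0.842√(p1(1 - p1) + p2(1 - p2))]²/(p1 - p2)², where p is the mean of p1 and p2.
- Continuity-corrected: n' = (n/4)[1 + √(1 + 4/(n|p1 - p2|))]².

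**Which formula produced the printed cells?** The first-year rows follow the rate formula. For example, 0.62 v 0.45 gives 290.6 (printed 291), and 0.40 v 0.30 gives 549.4 (printed 551). The second-year rows compare as follows:

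| Comparison | Printed | Corrected proportions | Rates |
|---|---|---|---|
| 6b, 0.62 v 0.86 | 59 | 59.3 | 201.7 |
| 6b, 0.62 v 0.74 | 252 | 252.4 | 741.3 |
| 6b, 0.86 v 0.74 | 190 | 189.5 | 872.1 |
| 6a, 0.40 v 0.56 | 295 | 164.1 | 294.3 |
| 6a, 0.40 v 0.48 | 628 | 627.9 | 1,079.2 |
| 6a, 0.56 v 0.48 | 636 | 635.8 | 1,275.4 |

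Five cells match only the proportion formula; 295 matches only the rate formula. Example by rates: 7.849 × 1.36/0.12² = 741.3, rounded up to 742.

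**Understatement.** 202/59 = 3.4; 742/252 = 2.9; 873/190 = 4.6; 1,080/628 = 1.7; 1,276/636 = 2.0.

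**Does the label of risk rescue the figures?** Converting by 1 - exp(-rate), 0.62, 0.86 and 0.74 become 0.462, 0.577 and 0.523. The proportion formula then needs 297, 1,060 and 1,334 without the continuity correction, and 314, 1,092 and 1,371 with it. The printed 59, 252 and 190 fail on this reading too.

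**Power at the high-transmission site, 288 per arm.** Power = Φ(|r1 - r2|/√((r1 + r2)/n) - 1.960).
- Mefloquine v placebo: Φ(3.348 - 1.960) = 92%.
- Lapdap or SP v placebo: Φ(1.746 - 1.960) = 42%.
- Mefloquine v Lapdap or SP: Φ(1.610 - 1.960) = 36%.

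Pooling both sites with a full second year and the planned rates gives about 76% for Lapdap v placebo after 10% loss.

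**Parasitaemia, Table 6a.** The uncorrected proportion formula gives 121, 294 and 906 (printed 121, 294 and 908). Footnote b halves mefloquine's 50% effect to 25%, and footnote e applies the clinical-malaria reduction to parasitaemia: 30% × 0.75 = 22.5%, not 20%. Table 6b follows the rule (40% × 0.75 = 30%). With 22.5%, the 294 becomes 540 and the 908 becomes 424.

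The prevalence at 10 months is not given, so a range is needed. Halving the placebo value for mefloquine:
- 4% v 2% needs 1,141 per arm, with about 49% power at 549.
- 10% v 5% (an assumed value) needs 435.

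**Isolates.** Section 4.11 takes 25% of 930, about 230. Tables 6a and 6b imply (610 × 30% + 320 × 40%)/930 = 33%. Section 3 gives 4% for South Pare infants. The three do not agree.

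**The case against.** The strongest reply is that nothing hangs on these rows. Enrolment is set by the primary outcome (551 and 291 per arm). Mefloquine v placebo keeps more than 90% power for rebound at each site on the planned rates (97% and 92%). Section 4.4 already cautions that placebo v Lapdap may be under-sized even with the sites combined, which agrees with the rate formula. All of this stands. What remains is that Table 6b prints 252, below the 288 evaluable, directly against that caution.

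Several stronger readings are tempting, and the protocol does not support them:
- **The whole second-year row is wrong.** It is not: 295 is the rate-formula value and should stay.
- **The 30% was copied from the 1-4-year-olds.** The figures coincide, but footnote c cites unpublished regional surveys without an age group, and Table 6b's 40% matches neither Western Usambara figure in Section 3 (52% and 20%). Nor is 4%, an average over all infants under one year, the prevalence at 10 months. The conflict is real; its cause is unknown.
- **The isolates should be about 88** (610 × 4% + 320 × 20%). The 20% belongs to Western Usambara, and Section 3.1 moved the high-transmission site to Lwengera, for which no infant prevalence is given. With Table 6b's 40% the sum would be 24 + 128 = 152.
- **Rebound is the trial's main safety question.** Section 4.8 assesses safety by haemoglobin change, a day 3 questionnaire and adverse-event reporting.
- **South Pare contributes only six months of the second year.** Section 4.5 ends scheduled visits at 18 months, but cases come from passive surveillance and Section 4.9 runs to 24 months. The protocol leaves this open.

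**Conclusion.** The point holds as a correction of secondary planning figures and stated power. Five of six second-year cells are too small by factors of 1.7 to 4.6. The high-transmission site alone is well powered for mefloquine v placebo (92%) but not for Lapdap or SP v placebo (42%) or mefloquine v Lapdap or SP (36%). The 20% in the Table 6a parasitaemia row contradicts footnotes b and e; correcting it raises one size (294 to 540) and lowers another (908 to 424). The 30% conflicts with the infant figure in Section 3, and the documents do not settle the right value.

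A reader might infer that the trial is too small or that enrolment must change; neither follows. The results assume two-sided 5% tests, the planned rates, 10% loss, one year at risk per child, and no variation in rate between children beyond Poisson, which would raise the sizes further. The South Pare and pooled figures also assume 0.40 per child-year in placebo, while Section 4.5 itself describes incidence there as low.

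**What to change.** - Restate the second-year rows by the rate formula: 202, 742 and 873 in Table 6b; 295, 1,080 and 1,276 in Table 6a. Label them as incidence per child-year.
- State the high-transmission site's power at 288 per arm (about 92%, 42% and 36%). Say that a null Lapdap or SP rebound result will be reported by its confidence interval and not as reassurance.
- Reconcile Section 4.4 (sites combined), Section 6 (sites separate), Section 4.5 (last South Pare scheduled visit at 18 months) and Section 4.9 (follow-up to 24 months), and state which person-time enters the rebound analysis.
- In the Table 6a parasitaemia row, use 22.5% for Lapdap and SP if 30% is kept (540 and 424). Give the source age group of the 30%, and show the row over an assumed range that includes 4% and 10%.
- Reconcile that range with the 25% behind the 230 isolates, without substituting another single count unless an infant prevalence for Lwengera is available.

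The cost is edits to tables and text. Enrolment and the primary sample sizes are untouched. Most of the restated second-year sizes are less favourable.

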**4.5. Screening, enrolment and follow up procedures**

All infants attending the EPI clinics at the study health centres for BCG or DPT&polio 1 vaccination (**contact 0**) will be screened for eligibility for enrolment into the study. The study objectives and procedures will be explained to caretakers of the infants who are eligible and they will be given an information sheet to take home. After obtaining written consent, the following procedures will be carried out: (1) collection of digital photos for a photo ID card; (2) completion of an enrolment form which will contain information on identification, address and other details useful for follow up at home, socio-economic status, use of bednets and other malaria prevention measures, clinical history and signs and anthropometric indicators.

A list of study infants due for DPT/Polio 2 vaccination in each study EPI clinic on a given date will be generated from the enrolment database a week prior to the scheduled date. A member of the project team will visit the homes of these infants and remind them to attend the scheduled EPI clinic.

When the study infants return for DPT& Polio 2 (**contact 1**) the following procedures will be carried out: (1) allocation of infants to one the four arms of the study; (2) administration of the first dose of the study drug and dispensation of the remaining two doses of drug to be given at home; (3) collection of blood samples for Hb, malaria parasite and blood spot for genetic markers of drug resistance parasites; (4) advice given to the caretakers to bring their children to the health facility if the child becomes ill before the next scheduled visit.

In both study areas, the first 200 children will be followed up on day 7 post-administration of IPTi first course (**contact 1a**) and a finger prick blood sample will be collected for determination of haemoglobin and preparation of blood film.

A list of study infants due for DPT/Polio 3 vaccination in each study EPI clinic on a given date will be generated from the contact 1 database a week prior to the scheduled date. A member of the project team will visit the homes of these infants and remind them to attend the scheduled EPI clinic.

When the study infants return for DPT& Polio 3 (**contact 2**) the following procedures will be carried out: (1) administration of the first dose of the second course of the study drugs and dispensation of the remaining two doses of drugs to be given at home; (2) advice given to the caretakers to bring their children to the health facility if the child becomes ill before the next scheduled visit.

A list of study infants due for measles vaccination in each study EPI clinic on a given date will be generated from the contact 2 database a week prior to the scheduled date. A member of the project team will visit the homes of these infants and remind them to attend the scheduled EPI clinic.

When the study infants return for measles (**contact 3**) the following procedures will be carried out: (1) administration of the first dose of the third course of the study drugs and dispensation of the remaining two doses of drugs to be given at home; (2) collection of blood samples for measles serology; (3) advice given to the caretakers to bring their children to the health facility if the child becomes ill.

In both study areas, the second 200 children will be followed up on day 7 post-administration of IPTi third course (**contact 3a**) and a finger prick blood sample will be collected for determination of haemoglobin and preparation of blood film.

A list of study infants who are due for blood examination one month after receiving course 3 of the study drugs will be generated from the contact 3 database every month. These infants will be invited to attend the clinic where they will be reviewed and **(contact 4)** a finger prick blood sample (400 μl) will be collected for determination of Hb, blood film preparation for malaria parasites and measuring anti-VSA antibodies.

A random sample of 20% of infants will be invited to attend the clinic at 11 months of age or two months after the 3rd course of the study drug (**contact 5**) and a finger prick blood sample will be collected for Hb and blood film preparation.

Another random sample of 20% of children will be invited to attend the clinic at 12 months of age or 3 months after the 3rd course of the drug (**contact 6**) and a finger prick blood will be collected for Hb and blood film preparation. Infant who had a blood sample taken at 11 months of age will be excluded from the sample of infants selected for collection of blood samples at 12 months of age.

All study children will be invited to attend the clinic at the age of approximately 18 months (**contact 7**) and a finger prick blood sample (400 μl) will be obtained for determination of Hb, blood film preparation for malaria parasites and measuring anti-VSA antibodies.

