**Figure 2**. **Study design**

**Contact 0**: Infants attend EPI clinics for BCG and/or DPT & Polio1 vaccines

1. identification of eligible infants

2. provision of information about the study to the care takers

3. enrolment of eligible infants after obtaining informed consent

2 months

Approximate age

**Contact 1:** Infants return for DPT 2 and Polio 2 vaccines

1. random allocation to one of the study groups

2. administration of the first course of treatment

3. collection of blood samples for Hb and blood film and filter paper

4. appointment for contact 2 (DPT and polio 3)

Group 1

placebo

Group 2:

Mefloquine

Group 3:

Lapdap

Group 4:

SP

Passive surveillance at health facilities for side effects of drugs, clinical malaria, and anaemia until 24 months of age

**Contact 2**: Infants attend EPI clinic for DPT 3 & Polio 3 vaccines

1. completion of data forms and administration of the second course of allocated drug

2. appointment for contact 3 (measles vaccine)

**Contact 3**: Infants attend EPI clinic for measles vaccine

1. completion of data forms and administration of the third course of allocated drug
2. collection of blood samples for baseline measles serology
3. appointment for contact 4 (1 month after the date of contact 3)

**Contact 4**: (1 month after the date of contact 3)

Collection of blood samples for Hb, blood film, post vaccine measles serology, and anti-VSA antibody assay

1 months

3 months

9 months

10 months

**Contact 5**: (20% random sample)

Collection of blood sample for Hb and blood film

**Contact 6**: (20% random sample)

Collection of blood sample for Hb and blood film

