**4.3. Outcome measures**

*Primary outcome measures*

1. Incidence of clinical malaria: [(history of fever during previous 2 days or axillary temperature >37.5ºC) + parasitaemia of any density + absence of any other obvious causes of fever] during the period of 2-11 months of age

*Secondary outcome measure*

1. Mean Hb at 10-12 months of age (one month after the third course of IPTi)
2. Incidence of severe anaemia (Hb <7 g/dl) during the period of 2-11 months of age
3. Prevalence of parasitaemia at 10-12 months of age (one month after the third course of IPTi)
4. Incidence of clinical malaria [as defined above] during the period of 12-23 months of age.
5. Level and repertoires of plasma antibodies to *plasmodium falciparum* variant surface antigen (anti-VSA antibodies) at 10 and 18 months of age.
6. EPI serology
7. Prevalence of G6PD deficiency and human haemoglobinopathies.

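### The 10-month blood sample (contact 4) is offered only to infants who received course 3, so three secondary outcomes are measured in a group selected after randomisation

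*Protocol*

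**What the plan says.** Figure 2 places "random allocation to one of the study groups" at contact 1 (DPT/polio 2). Contacts 2, 3 and 4 all follow randomisation.

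The lists in section 4.5 then run in a chain:

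- Contact 2 (course 2): the reminder list "will be generated from the contact 1 database a week prior to the scheduled date". This covers every randomised infant.
- Contact 3 (measles vaccine, course 3): the reminder list "will be generated from the contact 2 database a week prior to the scheduled date".
- Contact 4 (Hb, film, anti-VSA): infants due "one month after receiving course 3 of the study drugs will be generated from the contact 3 database".

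Figure 2 agrees: at contact 3 the caretaker receives an "appointment for contact 4 (1 month after the date of contact 3". Section 4.3 builds the same anchor into the endpoint, "Mean Hb at 10-12 months of age (one month after the third course of IPTi"; the parasitaemia outcome carries the same qualifier. The 10-month anti-VSA measurement uses the contact 4 sample.

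Other visits are not tied in this way. Contacts 5 and 6 (separate 20% random samples, Hb and film only) are timed by age (11 and 12 months) or by time since course 3. For contact 7, "All study children will be invited to attend the clinic at the age of approximately 18 months".

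**The concern.** Receiving course 3 is an event after randomisation. A comparison restricted to infants who received it is not a comparison of the randomised groups, and nothing in section 4.5 provides a 10-month sample for the others.

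Two things are at stake. First, the result describes infants who received course 3. If those without it are less protected, the effect in all randomised infants is smaller than the sample shows. Second, if attendance at contact 3 differs by arm and is related to Hb or parasitaemia, the contrast between arms is biased. Section 4.7 anticipates vomiting after mefloquine, and section 1.4 reports that Hb falls in G6PD-deficient children were more frequent on Lapdap than on SP, so arm-related default is possible. The t-test named in section 6 for mean Hb makes no allowance for it.

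**Working it through.** **The plan's own figures.** Table 6a gives 252 per arm for an Hb difference of 0.5 g/dl and 63 for 1.0 g/dl. With n = 2(1.96 + 0.842)²·SD²/δ² and SD = 2.0 g/dl, n = 2 × 7.85 × 4 / 0.25 ≈ 251.2, so 252; for δ = 1.0 it is 62.8, so 63. The SD is not stated; 2.0 is back-solved from the table. The parasitaemia sizes of 121 (30% v 15%) and 294 (30% v 20%) also reproduce. The sample sizes contain no error that bears on this point.

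**Effect on the parasitaemia result.** Inputs from Table 6a: placebo 30%, mefloquine 15%, so the sampled infants show a 50% reduction. Assumptions: a share m of randomised infants misses the sample, the same in both arms; mefloquine infants without course 3 have the placebo prevalence; placebo infants have 30% whether sampled or not.

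Prevalence in all mefloquine infants = (1 − m) × 15% + m × 30%. Reduction = 1 − prevalence/30%, which equals 50% × (1 − m).

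| Who is missed | m | Prevalence, all randomised | Reduction |
|---|---|---|---|
| Contact 3 defaulters, 5% | 5% | 15.75% | 47.5% |
| Contact 3 defaulters, 10% | 10% | 16.5% | 45% |
| Contact 3 defaulters, 15% | 15% | 17.25% | 42.5% |
| Upper case, 5% at each of contacts 2 and 3 | 9.75% | 16.5% | 45% |
| Upper case, 10% at each | 19% | 17.9% | 41% |
| Upper case, 15% at each | 27.75% | 19.2% | 36% |

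The upper case uses m = 1 − (1 − d)² and supposes that every infant who misses contact 2 also misses contact 3.

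**If attendance differs by arm.** Suppose non-attenders' Hb is D lower. The error in the Hb difference is D × (difference in attendance). With D = 1 g/dl (assumed) and attendance differing by 5, 10 or 20 percentage points, it is 0.05, 0.10 or 0.20 g/dl, which is 10%, 20% or 40% of the 0.5 g/dl target. With equal attendance and equal selection it is zero.

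**Precision.** Power for Hb 0.5 g/dl, SD 2.0, two-sided 5%:

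| Share sampled | South Pare (610 per arm) | High transmission site (320 per arm) |
|---|---|---|
| 90% | n = 549, 98.5% | n = 288, 85.1% |
| 80% | n = 488, 97.4% | n = 256, 80.7% |
| 70% | n = 427, 95.5% | n = 224, 75.4% |

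**The case against.** The list matches the endpoint as written: 4.3 defines outcomes 1 and 3 by time since course 3, and the choice of analysis set could be left to the analytical plan promised in section 6. The first part is true, but it means that the endpoint shares the restriction. The second does not help, because no plan can analyse a sample that was not taken.

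Several stronger readings are tempting, and the protocol does not support them.

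- A reader might infer that only infants who took all three courses are sampled. An infant who misses contact 2 loses a home reminder, not the right to come for measles vaccine and course 3. The restriction that binds is at contact 4.
- A reader might infer that nobody without course 3 is bled in the 10-12 month window. Contacts 5 and 6 can include such infants, but only as 20% samples at 11 and 12 months and without antibodies. They do not replace the 10-month sample.
- A reader might infer that the primary outcome is compromised. Clinical malaria is found by passive surveillance of all study infants (4.9), so its ascertainment does not depend on these lists.
- A reader might infer that the sample becomes too small. At South Pare, Hb power stays above 90% even with 60% sampled (92.2%).
- A reader might take differential attendance as established. Section 4.7 itself expects that vomiting may be infrequent in mostly asymptomatic infants, and nothing links it to a missed measles visit months later.

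Section 9 budgets for tracing defaulters, and Figure 2 has the next appointment given at each visit, so some missed contacts would be recovered. Neither gives a sampling rule for those who are not. Some defaulters will have died or moved, and no list recovers them.

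**Conclusion.** The point holds for secondary outcomes 1 and 3 and the 10-month part of 5. They are measured in contact 3 attenders who received course 3, not in the groups formed at contact 1, and the protocol states no other route to that sample.

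On assumed contact 3 default of 5% to 15%, with placebo-like prevalence in infants without course 3, the overstatement is modest: 50% against 47.5% to 42.5%. The figures of 45% to 36% apply only if every contact 2 defaulter is lost as well. These are illustrations, since the protocol gives neither default rates nor outcomes in defaulters. The size and direction of any bias from unequal attendance cannot be derived. At South Pare the issue is selection and not precision. At the high transmission site, Hb power would fall below 80% somewhere between 80% and 70% sampled. The change is worth making because it is cheap and removes a selection that is built into the procedure.

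**What to change.** In 4.5, generate the measles and 10-month lists from the contact 1 (randomisation) database by due date. Invite every randomised infant to contact 4 one month after course 3, or at 10 months of age if course 3 was missed; this lies inside the 10-12 month window of 4.3. State which sample counts if course 3 is given after a 10-month sample. Amend outcomes 1 and 3 in 4.3, and the contact 4 entry in Figure 2, to match. Compare Hb, parasitaemia and anti-VSA by randomised arm, with course 3 recipients as a sensitivity analysis. Measles serology can stay limited to vaccinated infants.

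The cost is a changed database query and extra invitations and finger pricks. With 2,440 + 1,280 = 3,720 infants and 5%, 10% or 15% missing contact 3, that is at most 186, 372 or 558 infants over both sites, fewer once deaths and migration are removed. No new procedure is needed. The observed effect may be somewhat smaller than in course 3 recipients alone.
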